### Data collection and management

The data collection and timeline are shown in Table 2.

At baseline the following data will be collected:
Demographics, including renal diagnosis, length of end stage kidney disease, dialysis vintage and previous transplantation.Comorbidity.MedicationPre-study AVF information (previous AVF, anatomic placement of current AVF, AVF vintage, number of interventions on previous and present AVF, cannulation technique, access flow, recirculation, ultrasound of the AVF (cross section in millimetre).Pre-study hemodialysis information: hemodialysis/hemodiafiltration, dialysis prescription, Kt/V, anticoagulants during hemodialysis, median blood flow rate, arterial and venous pressure, blood pressure and weight in the latest 3 hemodialysis treatments before baseline, nutritional status defined by the normalized protein catabolic rate.For newly created AVFs: acute or permanent CVC, preoperative vein diameter and peroperative accessflow.Pre-study side effects: cannulation pain (visual analog score), dialysis side effects, symptoms of steal syndrome.Blood samples: haemoglobin, haematocrit, thrombocytes, leucocytes, C-reactive peptide, urea, creatinine, albumin, INR, ionized calcium, phosphate, parathyroid hormone, 25-OH D_2_, fibroblast-growth-factor-23, up-uc-MGP.

Monthly, the following data will be collected:
Dialysis information: Dialysis prescription, Kt/V, intravenous iron since last visit, anticoagulant during hemodialysis.Side effects: Same as baseline and side effects of FIR

The ultrasound examination of the AVF will be performed with Transonic System Inc. HDO3 (Transonic, Ithaca, NY, USA) or Philips Affinity 70 G (Phillips, Andover MA, USA). Access flow and recirculation, will also be measured by Transonic System Inc. HDO3 or Philips Affinity 70 G. Cardiac output will be measured by Transonic System Inc. HCO3. Mobil-O-Graph (IEM, Stolberg, Germany) is used to measure the arterial stiffness.

### Sub studies

Two sub studies will be performed:
The acute effect of FIR on vasodilating and anti-inflammatory factors in the bloodThe acute effect of FIR on the blood pressure, access flow, skin temperature, arterial and venous pressure and cardiac output during a dialysis treatment

In study 1, 40 patients will have blood samples collected from their AVF before and after a FIR treatment/no FIR treatment. Another blood sample will be collected in the same time slot from the non-AVF arm. The following factors will be analysed: Serum Amyloid A, Vascular cell adhesion protein, Intercellular adhesion molecule, sE-selectin, Von Willebrand factor, Heme-Oxygenase 1, Nitric oxide products (nitrite, nitrate, asymmetric dimethylarginine), symmetric dimethylarginine, endothelin, Interleukins (IL6, IL8, IL-beta), Tumour necrosis factor alpha, Transforming growth factor beta and Monocyte chemoattractant protein 1. The samples will be kept in a − 80 degrees freezer. The patients will provide another written informed consent for this.

In study 2 the blood pressure will be measured every 5 min before, during and after FIR treatment/no treatment. Furthermore, access flow, recirculation and cardiac output will be measured before, during and after FIR treatment in a subgroup of 10 FIR treated patients and 10 controls.

The baseline data stated previously will be used for the above sub studies. All patients are dialysed on high flux filters. Furthermore, the following data will be collected on the study day: blood pressure, kilograms over dry weight, ultrafiltration volume, arterial and venous pressure, blood flow rate and day of dialysis during the week.

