### Outcomes

The primary endpoint for the prevalent AVFs is the difference in the overall patency rate between the treatment and control group after 12 months. The overall patency rate is defined as the AVFs without intervention and still in function after 1 year of treatment.

The secondary outcomes are the difference after 12 months in the treatment and control group in: access flow, number of abandoned AVF, change of vascular access to CVC or a new AVF, cardiac output, cannulation pain and number of patients with steal syndrome. Additional secondary outcomes are cardiac output and arterial stiffness at baseline as markers for AVF patency. Finally, the acute changes in the inflammatory and vasodilating factors after one FIR treatment will be compared to changes in the control group.

The primary endpoint for the incident AVFs is the time from placement of an AVF to successful cannulation (defined as a successful hemodialysis treatment with two fistula needles placed in the AVF). The secondary outcomes is the difference between the treatment and control group after 12 months in: number of interventions, diameter of the AVF measured by ultrasound, number of abandoned AVF, number of vascular access change (CVC or new AVF), number of primary patency, change in access flow, change in cardiac output, cannulation pain and number of patients with steal syndrome. Additional secondary outcomes are cardiac output and arterial stiffness at baseline as markers for AVF maturation and patency.

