#### Incident AVFs

Hemodialysis patients at the largest dialysis centre in Denmark have a mean of 100 days (SD ± 46) from placement of a new AVF to successful cannulation (defined as a successful HD session with two needles in the AVF). Several guidelines suggest cannulation of a new AVF to be 28–56 days after establishment [2, 3]. Therefore, the minimal relevant difference between the intervention and the control group, which we would like to detect is a decrease from 100 to 70 days before successful cannulation. With a power of 80% and a significance of 5% the number of patients needed for inclusion is 37 patients in each group. With an expected drop out of 20%, the overall number Is 81. Due to equal randomization the total number is 82.

Continuous variables will be expressed as mean ± SD when normally distributed and compared by paired and unpaired *t-test* as appropriate. Non-normally distributed variables will be described as median (range) and compared by Wilcoxon signed rank test and Mann-Whitney U test as appropriate. Categorical variables will be described as numbers and percentages and be analysed by Chi-squared test to compare differences between the intervention and control group.

Survival curves of patency will be calculated by the Kaplan-Meier method and compared by the log rank test. A *p*-value < 0.05 is considered significant.

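### Sub study 1 compares before-after changes in 17 blood factors by unadjusted tests under one blanket p < 0.05 rule with no lead factor; adjust for the pre-treatment level and report the panel as exploratory

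*Protocol article*

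**What the plan says.** The Sub studies section of the protocol article states that "40 patients will have blood samples collected from their AVF before and after a FIR treatment/no FIR treatment". A further sample is taken from the arm without the fistula. The list of analytes opens with "The following factors will be analysed: Serum Amyloid A, Vascular cell adhesion protein, Intercellular adhesion molecule" and in full runs:

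- "Serum Amyloid A, Vascular cell adhesion protein, Intercellular adhesion molecule, sE-selectin, Von Willebrand factor, Heme-Oxygenase 1" (6 factors)
- "Nitric oxide products (nitrite, nitrate, asymmetric dimethylarginine), symmetric dimethylarginine, endothelin" (5 factors)
- "Interleukins (IL6, IL8, IL-beta), Tumour necrosis factor alpha, Transforming growth factor beta and Monocyte chemoattractant protein 1" (6 factors)

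The Outcomes section places the comparison among the secondary outcomes for prevalent fistulas: "the acute changes in the inflammatory and vasodilating factors after one FIR treatment will be compared to changes in the control group". The Objectives section has it as the third of four aims, worded as an evaluation of whether FIR lowers inflammatory factors and raises vasodilating ones.

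The statistics text at the end of Sample size and statistics offers paired and unpaired t-tests, or their rank counterparts, for continuous variables. It closes with a single rule: a p-value "< 0.05 is considered significant". The rule is not limited to particular endpoints. No factor is singled out as the main one.

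Elsewhere (Abstract, end of Background, Discussion, Potential impact of the trial) the article says that these changes will be explored.

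**The concern.** There are two separate weaknesses in what the article fixes.

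1. **Reading the panel.** The third objective concerns two whole classes of factors. Nothing says which factor, or how many of them, would answer it, while the significance rule as worded covers each factor alone. A reader of the results could take one small p-value among 17 as evidence of a mechanism.
2. **Precision.** The comparison is of changes, and the named tests use the pre-treatment level only by subtracting it. With 40 patients, precision is scarce, and the sample needed for a more precise analysis is already being drawn.

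At stake is the mechanistic conclusion of the trial. The primary conclusions on maturation and patency do not depend on it.

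**Working it through.** The article gives no error rate, power or sample size derivation for this sub study, so it has no figure of its own to reproduce.

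**Inputs from the article**
- Factors: 6 + 5 + 6 = 17, counting bracketed items singly.
- Threshold: p < 0.05 for each test. Two-sided is assumed, as sidedness is not stated.
- Patients: 40. A split of 20 and 20 is assumed from the trial's 1:1 allocation.

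**Inputs not in the article (assumed ranges)**
- Correlation between factors: 0 to 0.8.
- Before-after correlation r within a factor: 0.5 and 0.8 as examples.

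**Chance of at least one false positive, AVF sample only, if FIR has no effect**

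Under independence: 1 − 0.95^17 = 1 − 0.418 = 0.582, or 58%. The expected number of false positives is 17 × 0.05 = 0.85, and correlation does not change this expectation.

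Correlation does lower the chance of at least one. The correlated cases were simulated with two-sided t-tests on change, 20 against 20, equal correlation between all pairs of factors and 10,000 trials per setting:

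| Correlation between factors | Chance of at least one p < 0.05 among 17 |
|---|---|
| 0 (formula) | 58% |
| 0.2 | about 54% |
| 0.3 | about 50% |
| 0.5 | about 39% |
| 0.8 | about 22% |

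The count matters little. If the nitric oxide products and the interleukins each counted as one, there would be 17 − 2 − 2 = 13 tests, and 1 − 0.95^13 = 0.487, or 49%, under independence.

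**Precision of the two analyses**

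Take equal variance σ² before and after treatment.
- Variance of a change score: 2σ²(1 − r).
- Variance after adjustment for the pre-treatment level: σ²(1 − r²).
- Ratio: (1 − r²) / [2(1 − r)] = (1 + r)/2.

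| r | Change score (σ² = 1) | Adjusted (σ² = 1) | Reduction |
|---|---|---|---|
| 0.5 | 1.00 | 0.75 | 25% |
| 0.8 | 0.40 | 0.36 | 10% |

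The ratio is below 1 for every r below 1. Estimating the slope costs one residual degree of freedom (37 instead of 38 with 40 patients), which takes back a little of the gain, chiefly when r is close to 1.

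**The case against.** **The work is exploratory and the article is condensed.** Several sections say that the changes will be explored, the work sits in a sub study, and multiplicity for such a panel is commonly left to an analysis plan that is not shown. This largely stands. The absence of a formal correction is not an error in itself, and reporting the panel as exploratory is sufficient. What remains is that the article does state a significance rule, without exempting these factors, and words the aim as an evaluation.

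**A false claim might be inferred to be more likely than not.** The documents do not support that. It needs FIR to affect no factor and the tests to be nearly independent, and at a correlation of about 0.3 the chance is already down to about one half. The list contains related items measured in the same blood samples, such as nitrite with nitrate and the two dimethylarginines. The objective is also directional. Counting only chance results in the favourable direction gives 1 − 0.975^17 = 0.350, or 35%, under independence.

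**The test count might be doubled for the two sampling sites.** The article does not say that the non-fistula arm is tested separately between groups; that sample may serve as a within-patient reference.

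**One significant factor might be thought enough to meet the objective.** No section says so. The point here is only that the article does not guard against that reading.

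**The sample size of 40** affects precision and power, not the false-positive rate.

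**Comparing changes is valid.** Between randomised groups it is unbiased, and the gain from adjustment depends on an r that the article does not give. Both statements are true. They make adjustment an improvement rather than the repair of an error, but it needs no new data.

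**Conclusion.** The concern holds as an optional improvement. The article puts 17 factors under a single p < 0.05 rule with no lead factor. If FIR had no effect, the chance of at least one p < 0.05 would lie between about 22% (correlation 0.8) and 58% (independence), which is more than four times the nominal 5% even at the lower end. A single significant factor therefore does not answer the third objective.

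Separately, the stated comparison of changes is valid but less precise than an analysis adjusted for the pre-treatment sample: the adjusted variance is 25% lower at r = 0.5 and 10% lower at r = 0.8. The ranges rest on assumed correlations, equal variances before and after, and a 20 and 20 split in the simulation. The primary endpoints are untouched.

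**What to change.** 1. For each factor, model the post-treatment level in the AVF sample (on the log scale if skewed) on arm, adjusted for the pre-treatment level.
2. Report all 17 estimates with 95% confidence intervals and label them exploratory, in line with the article's own description.
3. If any factor is to be called significant, control the false discovery rate at 5% over the 17 factors (Benjamini-Hochberg) and say so beforehand.

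The p < 0.05 rule for the other secondary outcomes need not change on account of this point.

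**Cost.** Steps 1 and 2 need a few sentences and no new data. Step 3 demands smaller p-values for isolated findings: a lone factor would have to reach 0.05/17 = 0.0029. With 20 per arm and a true difference of 1 SD, power for one factor by normal approximation falls from 89% at 0.05 to 57% at that strictest threshold. The loss is smaller when several factors respond together, because the later thresholds in the procedure are less strict.

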## Monitoring

Previous studies have shown very few side effects of the FIR treatment, such as burning and/or itching sensation. All the data collection will be performed during the patient’s regular hemodialysis treatment, thus there is no extra time for the participant to spend in the department due to the study. Blood samples will be drawn from the dialysis machine, so no extra needling of the patient is needed. Every third month the incidence of side effects will be evaluated. If there is a significant increased incidence in the intervention group (due to FIR) the study will be terminated and the participants will be informed.

Recruitment begun in October 2019. We expect to have completed recruitment in March 2021 for the group with prevalent AVF and in October 2022 for the group with incident AVF with the final data collection in April 2024.

## Discussion

The present study will examine the effect of FIR treatment on AVF maturation and overall patency rate through a randomized, multicenter, open-labelled trial. Furthermore, the acute effects of FIR in terms of changes in anti-inflammatory and vasodilating factors during FIR treatment will be explored and arterial stiffness as a marker for AVF maturation and patency will also be investigated.

After placement of an AVF there is a high risk of maturation failure and need of assisted patency [9, 10, 14]. Approximately 22 to 37% of created AVFs fails and will never be used. By 1 year, 40% of all AVFs fails or have required at least one intervention [10]. Maturation of the AVF depends on several patient related, but also surgically related factors. Factors such as comorbidity (diabetes mellitus, peripheral vascular disease), female sex, length of ESKD, anatomy of the vessel, surveillance after AVF placement, anatomic placement of the AVF and the surgically procedure itself have all been shown to have an influence on the AVF maturation [12, 13, 15, 28, 29].

Studies investigating possible therapies that improves the AVF maturation and survival are scarce. Since the dialysis population is getting older, they present with more comorbidities, and thereby an increased risk of AVF maturation failure. Therefore, there is a need of new interventions that may improve the AVF maturation. FIR is a suggested treatment modality with promising results in the presently available studies [22–24]. There is an urgent need of further studies to explore this treatment. Cannulation of the AVF is by several guidelines suggested to be between 28 to 56 days [2, 3]. However, a huge difference between countries is seen. Early cannulation of the AVF has in studies shown not to reduce the AVF survival [14, 30]. In the largest dialysis center in Zealand, Denmark we found a median time to cannulation of 100 days (SD ± 46) suggesting a poor maturation rate. Lin et al. [22] found a significant improvement in maturation within 1 year (defined in successful cannulation in 8 out of 12 dialysis treatments of a 30 day period) in the FIR treated group compared to the control group (82% vs 60%). The primary endpoint for incident AVFs chosen in our study is therefore time to successful cannulation after AVF placement. Since the FIR treatment is supposed to have a thermal effect increasing blood flow and angiogenesis, we also wish to explore the change of access flow, diameter of the AVF and possible change in cardiac output (perhaps due to the increased access flow in the FIR treatment group). A difference in 1 year patency rate is also examined, since FIR treatment also has shown to decrease the incidence of interventions [22, 23].

After placement of the AVF the patency rates are poor. Al-jaishi et al. and Almasri et al. [9, 10] found a primary patency rate after 1 year of 60–65%. The stenosis in the AVF emerges from an endothelial dysfunction, inflammation and smooth muscle cell proliferation leading to intimal hyperplasia and in the end stenosis [16, 17]. The molecular mechanism that are responsible for the intimal hyperplasia is not well established [16, 28, 31]. Factors, such as Nitric Oxide, Heme-Oxygenase, TNF-alpha and MCP-1 are all factors, that are suggested to be of importance to the AVF maturation and stenosis [16, 31].

There is a need for studies that investigate possible treatments, that may prevent the development of the stenosis and improve the patency of the AVF. Previous studies [18, 32] have explored the effect of different antiplatelet medications, fish oil and prednisolone on the AVF maturation and patency with disappointing results. FIR is suggested by ERBP to be a possible new beneficial treatment for both AVF maturation and patency, but the results of the present studies of the effect of FIR on AVF malfunction is divergent. The studies are also from only one research group and one dialysis unit. Therefore, we designed the present randomized controlled trial to examine the influence of FIR on AVF patency in a Danish population in multiple dialysis units. The primary endpoint for prevalent AVFs is therefore improvement in patency rate in the two groups.

Since peripheral vascular disease is a risk factor for non AVF maturation and AVF survival one can speculate, that arterial stiffness, measured by pulse wave velocity can be used as a prognostic marker for AVF maturation and survival. This has only been explored in a few studies [33–35]. In the studies there were no correlation between arterial stiffness measured by pulse wave velocity and AVF maturation. The follow up time were 6–8 weeks, thus primarily examining the primary failure and maturation of the AVF. Arterial stiffness at baseline as a predictor for long term AVF survival has not previously been explored. This will be clarified in the present study.

The possible mechanisms behind FIR is unraveled. The theory is both a direct vasodilatory effect and a release of various anti-inflammatory and vasodilating factors [20, 21]. FIR has shown positive effects on wound healing and phantom pain in the lower extremities suggesting an increased blood flow and angiogenesis [20]. FIRs effect on a few of the molecular factors involved in the AVF stenosis, have been studied in vitro by Lin et al. [21]. They found a stimulation of heme-oxygenase 1 in endothelial cells (a molecule involved in the relaxation of the smooth muscle cells in the endothelium of the vessels). A decrease of several anti-inflammatory factors, such as tumor necrosis factor and interleukin 8 was also found. There are no studies exploring the acute effect of FIR treatment on these biochemical markers in vivo in a hemodialysis population. This will be explored in the present study.

A large limitation in this study is, that it is not blinded either by investigator, patient or dialysis nurse. Unfortunately, this is not possible due to the size of the FIR emitter and the feeling of the FIR treatment (warm sensation). The majority of the participants enrolled will be of Caucasian origin, and thus the results may not be applicable in other ethnicities. The company, that produces the FIR machine advise, that the FIR treatment can be given during the whole dialysis treatment, except for the last hour (due to risk of prolonged time to hemostasis). In this study the patients will receive the FIR treatment in different time slots during a hemodialysis treatment. If this affects the results is unknown. The optimal timeslot for the FIR treatment during the dialysis session has not previously been investigated. Accessflow on the incident AVFs to determine AVF maturation and time to cannulation is not performed, since this is not standard procedure in the included dialysis units in the study. Other standard criteria’s according to a guideline is used, as described in the Methods and design section.

This project is designed to fill an unmet need regarding methods to investigate factors affecting AVF maturation and patency in an investigator initiated and driven study.

### Potential impact of the trial

All previous studies favours AVF before CVC and AVG, respectively [4–10, 14]. Due to the high risk of stenosis, thrombosis, infection, infection-related mortality and all-cause mortality in patients with AVG and CVC, the need of a well-functioning AVF is of great importance. FIR may be a new treatment modality, which can induce maturation of the AVF and prevent stenosis [22–24], but previous studies are small and single centre with divergent results. The present paper describes the protocol of a randomized, controlled, open-labeled multicenter clinical trial, which will explore if FIR treatment will improve AVF maturation and patency. The acute changes in anti-inflammatory and vasodilating factors will also be explored and this will increase our knowledge of the mechanism of the FIR treatment. Finally, arterial stiffness as a marker for AVF patency will be examined.

If FIR shows to be beneficial on early AVF maturation and AVF patency it will have a positive impact on dialysis patients and their AVF worldwide.

## Data Availability

Not applicable.

